### Sample size and power calculation

Mysore: The sample size of the Mysore study component is based on the previous stress-responses study carried out during 2011–2013 among the Parthenon cohort participants
^41^. The previous sample size was calculated based on the only available study in children on the association between birth weight and stress response
^15^. We estimated that our sample will have 80% power to detect an effect size of 2.9 nmol cortisol increase per kg increase in birth weight at 5% significance level. In the current study, we aim to follow-up all the children who had participated in the above study. This sample size will have 80% power at the 5% significance level to detect an association of 0.18 SD of a continuous outcome (eg. TWA salivary cortisol) per SD of an exposure (eg. birth weight).

Mumbai: The sample size calculation for the Mumbai component of the study is based on the Mysore sample size. The estimated sample size will be able to detect an association of 0.16 SD of a continuous outcome per SD of a continuous exposure, and will detect a difference in outcome of 0.23 SD between the intervention and the control arms.

Pune: As there are no earlier studies on the effect of current nutritional intervention on stress responses, we based the sample size for this study on the findings from comparison of effect size between the offspring of B12 deficient and normal B12 status mother. The estimated sample size will detect an association of 0.28 SD of a continuous outcome per SD of an exposure. The study will detect a difference of 0.56 SD in the outcome between the control and intervention group.

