## Abstract

**Background:** Early life nutrition may affect individuals’ susceptibility to adult non-communicable diseases (NCD). Psychological stress is a well-recognised NCD risk factor. Recent evidence suggests that impaired foetal nutrition alters neuro-endocrine pathways, and hypothalamic-pituitary-adrenal axis feedback systems, resulting in abnormal stress responses, and NCD risk. This study aims to examine adolescent cortisol and cardiovascular stress responses in relation to maternal nutrition and contemporaneous NCD risk markers.

**Methods**: The study sample will be drawn from three well-established birth cohorts in India; the Parthenon cohort, Mysore (N=550, age~20y), the SARAS KIDS prenatal intervention cohort, Mumbai (N=300, age~10-12y) and the Pune Rural Intervention in Young Adults/ PRIYA cohort, Pune (N=100, age~22y). We will perform the ‘Trier Social Stress Test (TSST)’, a well-accepted stress-test module which involves participants performing 5-minutes each of public speaking and mental arithmetic tasks in front of unfamiliar ‘judges’ (stressor). Repeated measures of salivary cortisol and autonomic cardiovascular outcomes relative to the stressor will be assessed. Measures of psychological stress, cognitive function, blood pressure, glucose-insulin metabolism and depression will be carried out. Mechanistic studies including DNA methylation in gluco-corticoid receptor (
*NR3C1*) and
*11β-HSD2* gene loci and neuroimaging will be carried out in a subsample. Qualitative interviews and focus group discussions in a subsample of the Parthenon cohort will explore the perception of stress and stressors among the youth.

We will convert repeated measures into time-weighted averages before analysis. We will carry out multivariable regression analysis to test the associations. We will further refine the analyses using the mixed-model regression and conditional analyses for the association with repeated measures.

**Ethics and dissemination:** This study has been approved by the research ethics committee of CSI Holdsworth Memorial Hospital, Mysore. The findings will be disseminated locally and at international meetings, and reports will be submitted to open access peer reviewed journals.

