^36^. The primary outcome was birth weight, but the study was designed to have enough power to study long-term effects on body composition, cardiometabolic risk markers and cognitive function in the children. The intervention was a daily snack (such as samosas and fritters) made from micronutrient-rich foods (milk, green leafy vegetables and fruit). Women in the control group received a similar snack made from foods of lower micronutrient content such as potato and onion. A total of 6513 women were randomised, 2291 women became pregnant, and 1962 delivered live singleton newborns during 2006–2012. The study showed that supplementation increased offspring birthweight among women of normal or high body mass index
^36^. The incidence of GDM was halved in the intervention mothers compared to controls
^37^.

SARAS KIDS is the ongoing follow-up study of the offspring born to these women. In the SRAVANA study, we will randomly select 150 offspring each from the maternal intervention and control groups and all available OGDM during early adolescence (~10–12y). We will measure NCD risk markers and stress responses. We will test the hypothesis that ‘prenatal nutritional supplementation normalises cortisol and cardiovascular stress responses, especially in OGDM’.

**The Pune Maternal Nutrition Study (PMNS)** was a community based observational study set up in rural Pune in 1993
^38^. Non-pregnant, married women were identified, and followed up until they became pregnant (N=797). Pregnant women were assessed for diet, micronutrient status and foetal growth. The 753 offspring formed the PMNS cohort, and had detailed anthropometry at birth and at 6-monthly intervals. Maternal undernutrition (low BMI and vitamin B12 status) was widespread in this population. Low B12 status in the mothers was associated with higher insulin resistance in the children.

The PMNS offspring are now part of a community-based intervention study (ISRCTN 32921044), with the hypothesis that physiological doses of micronutrient supplementation during adolescence/young adulthood will improve the birthweight, B12 status, and newborn and childhood body composition in the next generation

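### Mumbai's stated detectable difference of 0.23 SD between arms does not follow from 150 per arm; the figure is about 0.32 SD, and power at 0.23 SD is about 51%

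*Protocol article*

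**What the plan says.** For Mumbai, the section Study sample fixes the arms: "we will randomly select 150 offspring each from the maternal intervention and control groups and all available OGDM during early adolescence". The number of additional offspring of mothers with gestational diabetes (OGDM) is not given. The Abstract lists "the SARAS KIDS prenatal intervention cohort, Mumbai (N=300, age~10-12y".

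The section Sample size and power calculation gives two sensitivities for this sample. The first is for a continuous exposure: "The estimated sample size will be able to detect an association of 0.16 SD of a continuous outcome per SD of a continuous exposure". The second is for the randomised comparison: the sample "will detect a difference in outcome of 0.23 SD between the intervention and the control arms". The Mumbai paragraph states no power, significance level or sidedness of its own. It says only that "The sample size calculation for the Mumbai component of the study is based on the Mysore sample size", and for Mysore the text reads "This sample size will have 80% power at the 5% significance level to detect an association of 0.18 SD of a continuous outcome".

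For Pune, with about 50 per group, the section gives 0.28 SD per SD of exposure and then: "The study will detect a difference of 0.56 SD in the outcome between the control and intervention group".

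**The concern.** The two Mumbai figures describe the same sample, so they should be linked by a fixed factor, and they are not. A difference of 0.23 SD is also too small for 150 per arm under the power and significance level that the section uses elsewhere.

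This is the only sensitivity stated for objective 3, the randomised test of prenatal supplementation. A reader would credit the comparison with good power at 0.23 SD when an effect of that size would be detected about half the time. A null result in Mumbai could then be over-read as evidence against effects of that size. The section Ethics and dissemination says that the Mumbai committee has still to be approached, so that committee would also be shown the favourable figure.

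**Working it through.** **Inputs.** Mumbai 150 v 150, total 300 (Study sample; Abstract). Mysore about 250 in the stress-test subsample and Pune about 50 per group, total about 100 (Study sample). Power 80% and significance level 5% (Sample size and power calculation, stated for Mysore). *Assumed:* two-sided test, and the same power and level for Mumbai and Pune. Outcome SD = 1 on the standardised scale.

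**Formulas.** With k = 1.960 + 0.842 = 2.802:

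- association per SD of exposure: k/√N
- difference between two equal arms: k × √(2/n per arm)

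**Step 1: check the assumptions against the section's standardised figures.**

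| Figure | Calculation | Result | Stated |
|---|---|---|---|
| Mysore association, N = 250 | 2.802/√250 | 0.177 | 0.18 |
| Mumbai association, N = 300 | 2.802/√300 | 0.162 | 0.16 |
| Pune association, N = 100 | 2.802/√100 | 0.280 | 0.28 |
| Pune difference, 50 v 50 | 2.802 × √(2/50) | 0.560 | 0.56 |
| **Mumbai difference, 150 v 150** | 2.802 × √(2/150) | **0.323** | **0.23** |

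Four of the five reproduce; the Mumbai arm difference does not. The t-based value is 0.325. The unstandardised Mysore figure (2.9 nmol per kg) cannot be checked, because no SDs are given.

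**Step 2: power at the stated difference.** The standard error is √(2/150) = 0.1155. 0.23/0.1155 = 1.992, and 1.992 − 1.960 = 0.032, which gives power of 51.3% (t-based 51.0%).

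**Step 3: size needed for 0.23 SD.** n per arm = 2 × (2.802/0.23)² ≈ 297 (t-based 298), or about 594 in total against 300 planned. Rounding does not close the gap: 0.225 to 0.235 SD needs 311 down to 285 per arm.

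**Step 4: a check that needs no power or significance level.** A 1:1 binary exposure has SD 0.5, so the detectable difference is 1/0.5 = 2 times the detectable association per SD, whatever k is. Unequal arms make the factor larger. Pune: 0.56/0.28 = 2.00. Mumbai: 0.23/0.16 = 1.44, and rounding allows only 0.225/0.165 = 1.36 to 0.235/0.155 = 1.52.

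**Step 5: other settings for 150 per arm.**

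| Setting | Detectable difference (SD) |
|---|---|
| One-sided 5% (or two-sided 10%), 80% power | 0.287 |
| One-sided 5%, 90% power | 0.338 |
| Two-sided 5%, 90% power | 0.374 |

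None gives 0.23. The value does appear if 300 is entered as the number per arm, 2.802 × √(2/300) = 0.229, or if the factor 2 is dropped, 2.802/√150 = 0.229. It is also 0.32 with its digits reversed. The article does not show which of these happened, if any.

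**The case against.** **Power and level are inferred.** The article states 80% and 5% for Mysore only, so the Mumbai paragraph does not itself claim 80% power at 0.23 SD. This is fair and should be said. But the same settings reproduce the other four standardised figures, and Step 4 shows the conflict without them.

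**The extra OGDM enlarge the arms.** Their number is unknown, so 51% is exact only if none are added to the comparison. Power at 0.23 SD would be 54% with 160 per arm, 63% with 200 and 73% with 250. Reaching 80% would take about 147 more in each arm. The stated 0.16 SD implies a total of (2.802/0.16)² ≈ 307, or 288 to 327 allowing for rounding, so the calculation did not assume that many.

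**Adjustment could sharpen the comparison.** The outcome is a change from baseline and mixed models are planned, so a gain in precision is possible. To bring 0.23 SD within reach, a covariate would have to correlate √(1 − 150/297) ≈ 0.70 with the outcome. The article states no such assumption, and the parallel Pune figure uses none. A fuller protocol might contain one; as printed, the number has no support.

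**Little follows from the error.** The Mumbai size is tied to Mysore rather than to 0.23 SD, no decision rule uses the figure, and results will be read from estimates and intervals. If it is a misprint, the design calculation may have been sound. This limits the practical effect, but the only published sensitivity for the randomised comparison is still wrong.

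**Conclusion.** The concern holds. At 150 per arm the detectable difference is 0.32 SD (0.323 by the normal approximation, 0.325 t-based), about 1.4 times the stated 0.23 SD. These sizes rest on a two-sided 5% test, 80% power carried over from Mysore, an unadjusted comparison, no added OGDM and no losses; losses would lower power further. That the two Mumbai figures are incompatible rests on none of the assumptions about power, level or sidedness.

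**What to change.** In the Mumbai paragraph of Sample size and power calculation, replace 0.23 SD with 0.32 SD and state the basis: 80% power, two-sided 5%, 150 per arm, unadjusted. Say whether the additional OGDM enter the arm comparison.

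If a smaller figure is wanted, base it on a baseline-adjusted analysis and state the assumed correlation r between baseline and outcome, using 0.323 × √(1 − r²). As an illustration only, r = 0.5 gives 0.323 × 0.866 = 0.28 SD; the article gives no value for r.

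The cost is one number and a short statement of assumptions. The stated sensitivity becomes less favourable; recruitment and the analysis do not change.

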### Ethics and dissemination

We follow Indian Council of Medical research (ICMR) guidelines for the ethical conduct of biomedical research. We have already received approval for the entire study from the ethics review committee of CSI Holdsworth Memorial Hospital, the host institution. Ethical permission will be sought additionally from the institutional ethical review committees in Mumbai and Pune prior to the start of these study components.

The participants will be given written information and the study is explained verbally, either telephonically or by home visit by research assistants/health workers. The participants will be encouraged to ask questions before obtaining consent. Written informed consent will be obtained for adult participants, and from parents in case of children <18 years (Mumbai) before commencing data collection. Verbal assent will be obtained from the children. Consent for genomic samples will be taken specifically.

The data generated from this study will be shared with the scientific community at local, national and international conferences, and published in open access peer review journals. The major findings will be shared with the study participants and their families in lay terms through public engagement initiatives.

### Study status

The follow-up of the Mysore Parthenon cohort participants is currently underway. By the end of April 2018, 82 participants have completed the TSSTs and 309 participants have undergone OGTT and assessments for other secondary outcomes except cognitive function. Qualitative interviews have been carried out among 5 adolescents/young adults.

## Conclusion

Altered neuro-endocrine reactivity to stressful situations is a risk factor for cardiovascular and mental health disorders in humans. Previous studies in India and other parts of the world have shown consistent associations between impaired early life nutrition and increased risk of these disorders. There is limited evidence for a role of early nutritional programming of stress responses, though this is considered one of the pathways for increased adult disease risk. Micronutrient deficiencies, especially of one-carbon nutrients, are associated with psychological manifestations of stress in humans
^58^. However, there are no studies examining the effect of nutritional supplementation on physiological stress responses in young individuals. Our study attempts to fill gaps in this area of research and explore in detail behavioural, environmental, epigenetic and neurological aspects linking early nutritional exposure to variations in stress reactivity.

To our knowledge, this is the first study to explore the role of life course nutrition on adolescent stress responses in humans. The study will generate robust evidence for the role of intra-uterine nutritional imbalances in the development of NCDs through programming of abnormal stress responses. Capitalising on the existing intervention designs in two well-known Indian birth cohorts, it will determine whether 1) prenatal nutritional supplementation and 2) current nutritional supplementation mitigates abnormal stress responses in vulnerable adolescents. The secondary analysis of these data, along with the existing past data, will guide the development of multi-faceted interventions for reducing NCD risks through a life course approach.

## Declarations

### Ethics approval

The study has been approved by the Ethics Committee of the CSI Holdsworth Memorial Hospital, Mysore (June 2017; no. CSIHMH/ERU2017/1). The committee membership follows Indian Council of Medical Research guidelines and is composed of a total of nine members (2 clinicians, 3 scientists, 1 legal expert, 1 social scientist/spiritual leader, 1 academician and 1 lay person).

## Data availability

All data underlying the results are available as part of the article and no additional source data are required
